## Abstract

**Background:**

Physical inactivity increases the risk of many chronic diseases including coronary heart disease, type 2 diabetes and some cancers. It is recommended that adults should undertake at least 150 minutes of moderate intensity physical activity throughout the week but many adults do not achieve this. An opportunity for working adults to accumulate the recommended activity levels is through the daily commute.

**Methods:**

Employees will be recruited from workplaces in south-west England and south Wales. In the intervention arm, workplace Walk-to-Work promoters will be recruited and trained. Participating employees will receive Walk-to-Work materials and support will be provided through four contacts from the promoters over 10 weeks. Workplaces in the control arm will continue with their usual practice. The intervention will be evaluated by a cluster randomized controlled trial including economic and process evaluations. The primary outcome is daily minutes of moderate to vigorous physical activity (MVPA). Secondary outcomes are: overall physical activity; sedentary time; modal shift away from private car use during the commute; and physical activity/MVPA during the commute. Accelerometers, GPS receivers and travel diaries will be used at baseline and one year follow-up. Questionnaires will be used at baseline, immediately post intervention, and one year follow-up. The process evaluation will examine the context, delivery and response to the intervention from the perspectives of employers, Walk-to-Work promoters and employees using questionnaires, descriptive statistics, fieldnotes and interviews. A cost-consequence study will include employer, employee and health service costs and outcomes. Time and consumables used in implementing the intervention will be measured. Journey time, household commuting costs and expenses will be recorded using travel diaries to estimate costs to employees. Presenteeism, absenteeism, employee wellbeing and health service use will be recorded.

**Discussion:**

Compared with other forms of physical activity, walking is a popular, familiar and convenient, and the main option for increasing physical activity in sedentary populations. To our knowledge, this is the first full-scale randomised controlled trial to objectively measure (using accelerometers and GPS receivers) the effectiveness of a workplace intervention to promote walking during the commute to and from work.

**Trial registration:**

ISRCTN15009100 (10 December 2014).

## Background

Physical inactivity increases the risk of many chronic diseases including coronary heart disease, type 2 diabetes, obesity and some cancers [1]. It is currently recommended that adults should undertake at least 150 minutes of moderate intensity physical activity in bouts of 10 minutes or more throughout the week [1-3]. There are concerns that many adults in the United Kingdom and other high-income countries do not achieve this [1,3-5].

Increasing physical activity levels, particularly among the most inactive, is an important aim of current public health policy in the UK [1,6]. There is also increasing interest in the relationship between time spent sedentary and poor health outcomes [7] and consequently UK health guidelines recommend that adults should minimise the amount of time spent sedentary (sitting) in addition to increasing physical activity [1].

Adult obesity levels may be linked to travel behaviour, one indicator of which is that countries with highest levels of active travel tend to have the lowest obesity rates [8]. Walking is a carbon neutral mode of transport that has declined in recent decades in parallel with the growth in car use [1]. Walking has been described as the nearest activity to perfect exercise [9]. It is a popular, familiar, convenient and free form of exercise that can be incorporated into everyday life and sustained into older age. Even walking at a moderate pace of 5 km/h (3miles/h) expends sufficient energy to meet the definition of moderate intensity physical activity [10]. Hence there are compelling reasons to encourage people to walk more, not only to improve their health but to address the problems of climate change [11-14].

In the UK, there are substantial opportunities to increase walking by replacing short journeys undertaken by car. For example, the 2011 National Travel Survey showed 22% of all car trips were shorter than two miles in length, while 18% of trips of less than one mile were made by car [15]. An opportunity for working adults to accumulate the recommended moderate activity levels is through the daily commute and, in addition, replacing the car for short journeys is likely to reduce sedentary time. Experts in many World Health Organisation (WHO) countries agree that significant public health benefits can be realised through greater use of active transport modes [16]. Furthermore, cost benefit analysis for the UK Department for Transport suggests the ratio of benefits to costs are high [17].

A systematic review comparing direct versus self-report measures for assessing physical activity in adults found self-report measures provided were higher estimates of physical activity than objective measures in some cases and lower values in others [18]. This calls into question the reliability of self-report measures, and indicates there is no approach to correcting for self-report measures that will be valid in all cases. However, very few studies have objectively measured the contribution of walking, particularly walking to work, to adult physical activity levels and more evidence is needed [19].

Systematic reviews have examined the effectiveness of interventions to promote physical activity in general [20-23] but there is less evidence about how best to promote walking to work. Available systematic review evidence has focused on: interventions that promote walking; [24] interventions that promote walking and cycling as an alternative to car use [23], and; the effectiveness of workplace physical activity interventions [25]. NICE public health guidance on workplace health promotion concluded that although schemes exist to encourage employees to walk or cycle to work, little is known about their impact [26]. Few studies used robust data collection methods to measure the impact of workplace interventions on employees’ physical activity levels, with most using self-report. There was also a lack of information about how interventions are influenced by the size and type of workplace and the characteristics of employees.

In 2011 the National Institute for Health Research Public Health Research (NIHR-PHR) programme funded the Walk to Work feasibility study (Project 10/3001/04) which incorporated Phase I development of a behavioural intervention followed by a Phase II exploratory trial in 17 workplaces in Bristol [27,28]. The intervention was tested in small, medium-sized and large workplaces, used objective measures of physical activity, and included process evaluation and an assessment of costs. Results from the feasibility study demonstrated that the intervention and its evaluation were feasible and funding was granted for a full-scale cluster randomised controlled trial commencing 1 November 2014 for 33 months.

## Methods/Design

### Aim

The overall aim of the research is to examine the effectiveness and cost effectiveness of an employer-led scheme to increase walking during the commute.

### Study design and setting

The study is a multi-centre cluster randomised controlled trial in 84 workplaces in south-west England and south Wales, and incorporates process and economic evaluations. The intervention will be implemented in 42 workplaces; 42 workplaces will comprise the control arm.

### The intervention

Workplace ‘Walk-to-Work promoters’ will be identified (volunteers, or nominated by participating employers) and receive a half-day training package provided by public health and transport specialists about the benefits of walking during the commute and how to promote increased walking either by walking the entire route or mixing walking with other transport modes. The Walk-to-Work promoters will be given resource packs and trained to access relevant websites and toolkits. They will also be trained in the use of specific behaviour change techniques that form the basis of the intervention, including: providing information on the link between walking and health; prompting intention formation; identifying barriers to walking and ways to overcome them; prompting goal setting; prompting self-monitoring; identifying social support and encouragement; reviewing goals, and; relapse prevention. There is evidence that these techniques are effective in achieving behaviour change [29,30] and can be effectively delivered by non-specialists. Additional booklets will be provided for employers/managers with information and ideas of how the workplace can support increased walking during the daily commute.

Participating employees will be contacted by the Walk-to-Work promoter and given a Walk-to-Work pack including an information booklet, travel diary and pedometer. Goals for incorporating walking into the journey to and from work will be set. Further encouragement will be provided through four contacts from the Walk-to-Work promoter over the following 10 weeks (face-to-face, email or telephone as appropriate to the workplace size, resources and work routines). During this time the Walk-to-Work promoters will also be prompted and encouraged in their role by four email/telephone contacts from the research team.

### Assessment of harms

This is a low risk intervention and there were no reported adverse events during the feasibility study. However, participants will be encouraged to report adverse and serious adverse events. These may relate to road traffic injuries and collisions; personal safety of walkers; difficulties experienced by Walk-to-Work promoters, including disrupting usual working relationships and employers attitudes towards time taken out of usual work activities; and costs to employers, including disruption to work routines, of permitting the intervention during working hours. If adverse events are attributable to the intervention, other relevant participants will be informed immediately e.g. other employees taking a similar route. It is also possible that people with low activity and no history of walking will suffer initial muscle stiffness. In most cases this would be mild and is a normal consequence of increased physical activity. However, participants will be given information about symptoms which may require medical attention and temporary or permanent cessation of walking to work. Such incidents will be recorded and monitored throughout the trial.

### The control group

The control group will participate in the baseline and one year follow-up data collection activities. No promoters will be trained in the control workplaces but they may be exposed to other workplace, local or national walking initiatives during the intervention period. Information about involvement in such activities will be collected through the questionnaires at baseline, post-intervention and one year follow-up.

### Inclusion and exclusion criteria

Employees in participating workplaces in south-west England and south Wales will be eligible to take part. However, employees who already always walk or cycle to work, who are due to retire before the one year follow-up data collection, or who are disabled in relation to walking, will be excluded. Employees for whom daily driving is a key part of their role (for example, sales representatives) will also be excluded. Workplaces with a large proportion of staff on short-term or zero-hours contracts are not suited because a high proportion of these people will move on before the one-year follow-up data collection. In addition, workplaces with firm plans to significantly downsize or relocate during the study period will be excluded.

### Recruitment of workplaces

There will be two rounds of recruitment, during February and March 2015 and again in February to March 2016. Workplaces will be approached through the local Chambers of Commerce and other employer organisations, and will be sent basic information about the study and an invitation to participate.

### Allocation and randomisation

Randomisation will take place at the level of the workplace. Employers in workplaces expressing an interest will be asked to complete a short questionnaire to broadly ‘match’ pairs of workplaces with respect to: size (1–10, 50, 51–250 or 250+ employees); [31] location (urban or suburban), and; type of business (for example, office-based, manufacturing). Assignment of workplaces to the intervention group, within each matched pair, will employ concealed computer generated allocation by an independent researcher from Bristol Randomised Trials Collaboration to minimise selection bias. It is not possible to blind participants following randomisation for this intervention.

### Participant recruitment

Information and leaflets and invitations to participate in the study will be distributed to employees by the employers using their usual mode of contact, for example, by email, attachments to wage slips, in pigeonholes or during team meetings. This will vary by size and type of workplace and will be noted as part of the process evaluation.

### Primary and secondary outcomes

The primary outcome, measured at baseline and one year follow-up, is daily minutes of moderate to vigorous physical activity (MVPA), with secondary outcomes of overall levels of physical activity (counts per minute (cpm)), and modal shift (number of days, over the previous five working days, when walking was the major mode of travel to/from work). The process evaluation will focus on: facilitators and barriers to workplace/employer participation in walk to work interventions; facilitators and barriers to employees walking during the daily commute, and; physical activity/MVPA due to walking during the journey to/from work. The economic evaluation will examine: costs to employers and employees of implementing the Walk-to-Work scheme; consequences for the employer (absenteeism/presenteeism); consequences for employees (commuting costs and wellbeing), and consequences for the public sector (health service use).

### Assessment and follow-up

Before randomisation, participating employees will be asked to complete a baseline questionnaire giving basic personal data (sex, age, ethnicity), job title, mode of transport to work, before and after work ‘routines’ affecting travel mode (for example, taking young children to school), typical commuting costs, household car ownership, commute related adverse events, health service use, wellbeing (ICECAP-A [32],) and views about walking. They will also be asked to wear an accelerometer for seven days from waking in the morning until going to bed at night to provide an objective measurement of physical activity (including intensity), and to carry a personal global positioning system (GPS) receiver from leaving home until returning from work. Participants will also be asked to complete a travel diary, recording mode of travel, costs and journey times at baseline and one year follow-up.

Immediately after the 10-week intervention, questionnaires will be administered in intervention and control arms to explore: attitudes towards, and experiences of, walking during the daily commute including perceived barriers and facilitators, and emotional and physical well-being. Additional questions about the acceptability of the intervention will be included for the intervention arm only. At one year follow-up questionnaires, accelerometers and GPS receivers, and travel diaries will be administered in intervention and control arms (as per baseline protocol).

The costs of the intervention to employers will be assessed by recording all time spent on training the promoters, implementing the intervention among employees, and materials or resources used. Absenteeism will be monitored using both the self-reported workplace productivity and impairment (WPAI) questionnaire [33] and anonymized data from workplace human resource systems where available. Costs to participants will be assessed by recording journey time, household commuting costs and expenses at baseline and one year follow-up using travel diaries. Self-reported measures of health service use will allow us to provide preliminary evidence on the savings or costs to the wider society. Employee wellbeing will be measured using ICECAP-A [32], a recently developed broader measure of benefit for use in economic evaluations of population health and other interventions.

### Measuring physical activity

The accelerometer will generate measures of physical activity. GPS data will be time-matched with accelerometer data and visualised in a geographic information system (GIS). Journeys to and from work will be identified and the data segmented to provide a measure of duration of the journey to work and associated physical activity. Validated accelerometer thresholds will be used to compute daily time spent in MVPA and sedentary.

### Process evaluation

The process evaluation will examine the context, delivery and response to the intervention from the perspectives of employers, Walk-to-Work promoters and employees. Interviews will be conducted immediately post intervention with a purposive sample of employees who have increased walking during the commute (n = 18), and employees who have not (n = 18). The sample will be stratified by workplace characteristics and gender. A purposive sample of employers (n = 12) and Walk-to-Work promoters (n = 12) will also be interviewed. Data relating to recruitment and retention rates, and responses to questions about the intervention and travel mode in the behavioural questionnaires, will also contribute to the process evaluation.

### Sample size and power calculations

Using findings from the feasibility study, the sample size for the full-scale trial was based on an average cluster size of 8, an ICC of 0.15, and participant attrition of 25%. With a total sample size of 678 we have 80% power with a 5% significance level to detect a 15% increase in mean MVPA.

### Statistical analyses

A full plan of the primary, secondary and economic analyses will be written prior to the study statistician being unblinded. Analysis of the primary outcome (MVPA) will be based on the data from the one year follow-up, with each individual kept in the study arm to which their workplace was allocated, irrespective of whether they engaged with the intervention. This will be supplemented with a sensitivity analysis, where missing outcome data are imputed. These analyses will be as close as possible to a full intention to treat analysis.

The treatment effect will be estimated with its 95% confidence interval using regression methods, which will allow any between-workplace variation in outcome to be incorporated as a random effect (an equivalent approach to multi-level modelling), and will allow the minimisation variables to be included as covariates. In addition baseline MVPA and imbalanced baseline measures will also be included as covariates, according to a process pre-specified in the study statistical analysis plan. Linear regression will be employed in the analysis of MVPA, and ordered logistic regression in the analysis of the number of days, over the previous five working days, when walking was the major mode of travel to and from work. If there is concern that a skewed MVPA distribution is causing problems for the linear regression, this will be investigated in a sensitivity analysis of log-transformed MVPA.

This approach will be adapted and repeated for secondary outcome measures, and the post-treatment measures. Evidence of differences in the treatment effect between groups of participants defined by, in turn, age, sex, and socio-economic status will be quantified by interaction tests. Additional sub-group analyses will be pre-specified in the statistical analysis plan, but only cautious conclusions will be drawn from these as they are likely to have low statistical power. Analyses of temporal patterns of activity and of the characteristics of participant’s journeys to work will be clearly presented as exploratory in nature.

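### The primary MVPA model adds whichever baseline measures prove imbalanced, so its covariates are not fixed until the arms are compared; a short list named in advance on prognostic grounds would be a cheap improvement

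*Protocol article*

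**What the plan says.** The Statistical analyses section of the protocol article describes one main regression for MVPA at one year, with a random workplace effect. Three kinds of covariate enter it.

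- Allocation variables: the model "will allow the minimisation variables to be included as covariates". I read these as the workplace matching factors under Allocation and randomisation. That section describes matched pairs rather than minimisation, which is a separate matter of wording.
- Baseline MVPA, always included.
- Measures found imbalanced: "In addition baseline MVPA and imbalanced baseline measures will also be included as covariates, according to a process pre-specified" in the statistical analysis plan.

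The third item belongs to the main model. The same section uses the sensitivity-analysis label for imputation and for log-transformation, but not here. On timing it says: "A full plan of the primary, secondary and economic analyses will be written prior to the study statistician being unblinded". The article gives no criterion for imbalance and may properly leave that to the plan.

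Under Assessment and follow-up, the candidate measures are collected before allocation: "Before randomisation, participating employees will be asked to complete a baseline questionnaire giving basic personal data (sex, age, ethnicity), job title", followed by travel, cost, health and attitude items.

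**The concern.** Adjusting for a covariate helps when it predicts the outcome. Imbalance between randomised arms is a different property. With baseline data collected before a concealed allocation, any difference between the arms as randomised is chance, and its size says nothing about prognostic value. Selecting on imbalance can therefore leave out a useful predictor that happens to be balanced, or bring in an uninformative one that happens not to be.

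The article leaves only the criterion to the analysis plan. It has already settled the principle, namely selection on observed imbalance, so a plan that follows this sentence must contain such a step. At stake are some efficiency and having a primary model whose covariates are known before the arms are compared.

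**Working it through.** **1. The plan's own figure.** The total of 678 cannot be reproduced, because no mean or SD of MVPA is given. It can be turned into a detectable standardised difference, assuming a two-sided 5% test and 80% power:

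detectable difference = (1.96 + 0.84) × √(2 / n_eff), where n_eff = (n per arm) / [1 + (m − 1) × 0.15].

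- 678 recruited with 25% lost: 678 × 0.75 / 2 = 254.25 per arm. With m = 8 the design effect is 2.05, n_eff = 124.0 and the difference is 0.356 SD. With m = 8 × 0.75 = 6 the design effect is 1.75, n_eff = 145.3 and the difference is 0.329 SD.
- 678 analysed: 339 per arm, giving 0.308 SD (m = 8) or 0.285 SD (m = 6).

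The range is 0.285 to 0.356 SD. No stated figure is shown to be wrong. The simulation below uses 0.29 SD.

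**2. How often a measure is flagged.** This depends on a criterion that the article does not state. For an assumed 5% test on K independent measures, P(at least one flagged) = 1 − 0.95^K. With K = 8 it is 1 − 0.663 = 34%. With K = 12, roughly the number of non-MVPA items listed at baseline, it is 1 − 0.540 = 46%.

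**3. Effect on the primary analysis.** I simulated 84 workplaces (42 per arm) with 6 analysed in each, an outcome ICC of 0.15 and a random workplace effect, with 3,000 runs per setting. Assumptions not in the article: eight independent candidate covariates with ICC 0.05, a baseline–outcome correlation of 0.5, and simple 1:1 allocation without pairing. Baseline MVPA was in every model. Two screens were tried: p < 0.05 on workplace means, and a standardised difference above 0.1.

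| Coefficient of each covariate | Screen | Power: baseline MVPA only | Power: screened | Power: all eight fixed | Screened minus fixed (points) | Type I error, screened |
|---|---|---|---|---|---|---|
| 0 | p < 0.05 | 0.788 | 0.787 | 0.787 | 0.0 | 0.049 |
| 0 | > 0.1 SD | 0.801 | 0.801 | 0.802 | −0.1 | 0.053 |
| 0.1 | p < 0.05 | 0.808 | 0.806 | 0.835 | −2.9 | 0.046 |
| 0.1 | > 0.1 SD | 0.810 | 0.818 | 0.831 | −1.3 | 0.051 |
| 0.2 | p < 0.05 | 0.850 | 0.862 | 0.955 | −9.3 | 0.042 |
| 0.2 | > 0.1 SD | 0.846 | 0.905 | 0.960 | −5.5 | 0.030 |

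Monte Carlo error is about 0.004 for type I error and up to about 0.007 for power.

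- Against baseline MVPA alone, screening changed power by −0.2 to +5.9 points (0.806 − 0.808; 0.905 − 0.846).
- Bias of the screened estimate was at most 0.004 SD.
- At least one covariate was flagged in 32–35% of trials with the p < 0.05 screen and in about 95% with the 0.1 SD screen.
- When one was flagged, the estimate moved on average 0.07–0.08 SE (coefficient 0), 0.21–0.24 SE (0.1) or 0.43–0.51 SE (0.2) from the estimate adjusted for baseline MVPA only.

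The last setting is demanding. Eight coefficients of 0.2 explain 8 × 0.2² = 32% of outcome variance on top of the 25% from baseline MVPA. Eight of 0.1 explain 8%.

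**The case against.** The strongest reply is that the article already fixes what matters most. Baseline MVPA, likely the main predictor, and the allocation variables enter regardless of imbalance. The rest follows a process written before unblinding, and that process might restrict candidates to sensible prognostic variables. This stands as a limit on the size of the problem. It does not make the covariate set known in advance.

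Three stronger readings are tempting, and the documents do not support them.

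- *That the interval or test is invalid because selection is ignored.* The screened test had type I error of 0.030 to 0.053, nominal or conservative, with negligible bias.
- *That the rule takes the trial below its planned power.* Screening lost nothing beyond simulation error against baseline MVPA alone. The shortfall is a forgone gain relative to a fixed list, and its size rests on prognostic strengths that the article does not give.
- *That measures will be flagged in most trials because the check ignores clustering.* With a design effect of 2.05 for every measure, a naive 5% test would flag each with probability P(|Z| > 1.96/√2.05) = 17.1%, and at least one of twelve in 1 − 0.829^12 = 89%. But the article names no test, no threshold and no unclustered check, and gives no covariate ICCs. The twelve measures are also not independent: travel mode, commuting cost and car ownership are plainly related. The same dependence makes the 34–46% above illustrative.

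One further point stands. Imbalance is purely chance only among everyone randomised. The primary analysis uses one-year data, with 25% attrition expected and participants not blinded. Imbalance among those followed up may reflect differential loss, and adjusting for it may then be useful. That supports keeping such an adjustment, but as a sensitivity analysis.

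**Conclusion.** The point holds in a limited form. The article commits the primary MVPA model to covariates chosen by observed imbalance, so the model is not settled until the arms are compared, and the selection principle is unrelated to prognostic value. Validity is not affected.

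The cost, relative to always adjusting for the same covariates, is between nothing and about 9 points of power: none if they are non-prognostic, about 1 to 3 if weakly prognostic, and 5 to 9 if eight are each more strongly prognostic. When a measure is flagged, the estimate moves on average by about 0.1 to 0.5 SE. These sizes rest on the assumed number, independence, ICC and strength of the covariates and on two illustrative screens. In no setting did screening beat the fixed list beyond simulation error. This is a cheap improvement.

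**What to change.** In the Statistical analyses section, and correspondingly in the analysis plan:

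1. Remove imbalance as a reason for entering the primary model.
2. Keep baseline MVPA and the allocation variables.
3. Name in advance a short list of further covariates, chosen on prognostic grounds from those already collected before randomisation; age, sex and baseline travel mode are examples.
4. Move adjustment for imbalanced measures, including imbalance among those followed up, to a labelled sensitivity analysis.

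This is about one sentence of text and needs no new data. The downside is a few degrees of freedom, which 84 workplaces can bear. The change should be made before the statistician is unblinded.
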